**1.INTRODUCTION**

Primary angioplasty (PA) is the reperfusion therapy of choice in ST-segment elevation myocardial infarction (STEMI)^1,2^. Several studies have shown a significant reduction in major adverse cardiac events (MACE) compared to fibrinolysis as a reperfusion strategy^3,4^.

About 40-50% of patients with STEMI have multivessel disease (MVD)^5^, defined as at least one angiographic stenosis greater than or equal to 50-70% in a vessel larger than 2 mm in diameter other than the vessel responsible for the STEMI and amenable to revascularization. These patients constitute a high-risk subgroup with a worse short- and long-term prognosis compared to patients with single-vessel disease^6^.

The 2012 European Society of Cardiology clinical practice guidelines for the management of STEMI patients, establish percutaneous coronary intervention (PCI) limited to the culprit vessel during PA with a class IIa recommendation, with multivessel revascularization only considered in case of haemodynamic instability^7^. This indication is mainly based on retrospective studies^8^ and meta-analyses^9^ where complete revascularization (CR) during PA was associated with increased mortality compared to both a conservative strategy of revascularization of the culprit vessel only and a more aggressive strategy of deferred CR of the non-culprit stenosis. The latter strategy of delayed multivessel revascularization has been associated with the greatest reduction in MACE during follow-up.

In recent years, 4 clinical trials PRAMI^10^, CULPRIT^11^, DANAMI 3 PRIMULTI^12^ and COMPARE-ACUTE^13^ have been published, comparing a strategy of revascularization of the culprit vessel only with a strategy of preventive CR or guided by analysis of fractional flow reserve (FFR).

The PRAMI study enrolled 465 patients with MVO, defined as the presence of angiographic stenosis ≥ 50% in non-culprit vessel. They were randomised 1:1 to PA of the culprit vessel and medical treatment of the remaining stenosis vs. percutaneous treatment of all stenoses during PA. This study was stopped early because of a significant difference in the primary endpoint (death, infarction, need for repeat revascularization) in favour of CR. A 65% relative reduction in the risk of the combined event was observed mainly due to a reduction in the incidence of angina and/or infarction, and need for repeat revascularization. However, no differences in total mortality during follow-up were observed between the two groups.

Later, the CULPRIT study compared the same revascularization strategies as the PRAMI study, however the presence of angiographic stenosis ≥ 70% in a non-culprit vessel was considered MVO. The study included 296 patients randomised 1:1 to both strategies, with the timing of CR left to the operator's discretion; CR was deferred to a second procedure in 27% of patients. Similar to the PRAMI study, a benefit of CR was observed with a significant reduction in the primary endpoint (death, myocardial infarction, heart failure, and need for repeat revascularization). However, although there is a trend towards a lower incidence of each of the in-hospital events, statistical significance was not reached for any of them separately.

Later the DANAMI-3 PRIMULTI study and recently the COMPARE ACUTE study found that FFR-guided CR was associated with a significant reduction in the risk of MACE compared to revascularization of only the culprit vessel.

These results prompted a modification of the American Society of Cardiology guidelines in 2015 from a class III recommendation to IIb for revascularization of non-culprit lesions during PA in haemodynamically stable patients^14^. Similarly, the recent European Society of Cardiology guidelines for the management of ST-elevation acute myocardial infarction establish a class IIa recommendation for routine revascularization of non-culprit lesions before hospital discharge, without establishing the optimal time for this to be performed.

All the aforementioned studies compare a strategy of CR with a strategy of treatment of only the culprit vessel and medical treatment of the remaining stenosis. In all of them, a significant reduction of the combined target was observed, mainly due to a decrease in the need for repeat revascularization. However, to date, there is no randomised study comparing two complete revascularization strategies performed at different times, with only retrospective studies of small size available. Politi et al^16^ randomised 214 patients to three different revascularization strategies; immediate revascularization during PA, delayed revascularization after hospital discharge and revascularization limited to the culprit vessel. A higher incidence of MACE was observed in the more conservative strategy limited to PCI of the culprit vessel (50%) compared to 20% and 23% in the other 2 CR strategies. This reduction in the risk of MACE with the preventive revascularization strategies was maintained in multivariate analysis after adjustment for multiple variables, with a risk reduction of 63% and 60%, respectively, with no differences between the two CR strategies.

In a retrospective study conducted at our centre, 807 patients undergoing PA from January 2009 to December 2015 were analysed. 398 (49.3%) patients showed MVD on coronary angiography, considered as the existence of at least one angiographic stenosis ≥70% in non-culprit vessel, of which 187 underwent only revascularization of the culprit vessel and 184 underwent preventive CR, 45 of them during PA. Of the 139 patients undergoing deferred CR, 69 (49.6%) were performed during the index admission and 70 (50.4%) in a second procedure on an outpatient basis after hospital discharge. During a median follow-up of 10.5 months (interquartile range: 5-30) no significant differences in all-cause mortality, cardiac death, reinfarction or readmission for heart failure were observed. However, an increase in total days of hospital stay was observed in patients undergoing complete revascularization during the index admission (8.2 ± 4 vs. 6.5 ± 2.9; p<0.001).

In the recent clinical practice guidelines of the European Society of Cardiology, on the management of patients with STEMI, for the first time establishes a class of recommendation for early discharge (48-72 hours) of low-risk patients undergoing PA. The PAMI II^17^ criteria for identifying low-risk patients include age <75 years, left ventricular ejection fraction greater than 45%, successful PCI and one- or two-vessel disease, so the existence of stenosis in non-culprit vessels is not a priori a high-risk criterion. However, a strategy of complete in-hospital revascularization could lead to an increase in the total length of stay of our patients, preventing early discharge as recommended by current clinical practice guidelines.

**2. STUDY DESIGN**

2.1. SUMMARY OF THE STUDY DESIGN

This is a prospective randomised single centre study. The study will be conducted in accordance with the principles set out in the Declaration of Helsinki (1996) and the International Conference on Harmonisation of Good Clinical Practice.

2.2 HYPOTHESIS

Complete outpatient revascularization of non-culprit lesions in patients with multivessel disease undergoing primary angioplasty significantly reduces hospital stay compared to in-hospital revascularization for the index event and is at least as safe a strategy.

2.3 PRIMARY OUTCOME

1º. To determine a reduction in hospital stay among patients undergoing complete revascularization during the index admission and on an outpatient basis.

2.4 SECONDARY OUTCOMES

1º. To determine the non-inferiority of the strategy of complete outpatient revascularization in reducing the combined safety event (death, reinfarction, need for repeat revascularization) at 6 and 12 months follow-up.

To assess the presence of ischaemia by analysing the fractional flow reserve of angiographically moderate stenoses (≥50% and <70%) in proximal segments of the anterior descending, circumflex or right coronary artery.

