**5. SAMPLE SIZE CALCULATION AND STATISTICAL ANALYSIS.**

5.1 Sample size calculation

The calculation of the sample size was based on the mean length of stay between the two strategies obtained in retrospective studies^18-19^ using the Stata 13 "sampsi" programme. Assuming a statistical power of 95% and a significance level of 5%, the sample size for each group is estimated at 110 patients. Taking into account loss to follow-up, the sample size has been increased by 15%, so that 125 patients will be included in each strategy.

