5.2 Statistical analysis

Quantitative variables will be expressed as mean ± 1 standard deviation, or as median (interquartile ranges) in the absence of Gaussian distribution. Discrete variables shall be expressed with the frequency distribution. Continuous variables shall be compared with Student's t-test. Discrete variables shall be compared with the X2 test. In all cases a p<0.05 will be considered significant. The statistical package STATA 13.1 will be used for data analysis.

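### The safety aim is non-inferiority, but the only stated analysis is a chi-square test of difference at p<0.05, with no margin

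*Protocol*

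**What the plan says.** The hypothesis in section 2.2 has two parts: after-discharge revascularization shortens hospital stay, "and is at least as safe a strategy". Section 2.3 makes length of stay the only primary outcome. Section 2.4 turns the second part into a formal aim: "To determine the non-inferiority of the strategy of complete outpatient revascularization in reducing the combined safety event (death, reinfarction, need for repeat revascularization"), to be assessed "at 6 and 12 months follow-up".

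Section 5.2 gives the analysis. For categorical outcomes it reads: "Discrete variables shall be compared with the X2 test. In all cases a p<0.05 will be considered significant". It makes no exception for the non-inferiority aim.

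On size, section 5.1 states: "The calculation of the sample size was based on the mean length of stay between the two strategies". It arrives at 110 per group, raised to 125 for loss to follow-up. The protocol gives no non-inferiority margin, no expected rate for the composite and no rule for declaring non-inferiority.

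**The concern.** The chi-square test takes equal risks as its null hypothesis. Non-inferiority asks whether any excess risk in the after-discharge arm is smaller than a tolerable amount stated beforehand. Without that amount the question is not defined, and a test of equality does not address it. A p-value above 0.05 means only that no difference was detected, and that becomes more likely as the trial gets smaller.

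The safety half of the hypothesis is at stake. A shorter stay argues for the after-discharge strategy only if safety is credibly shown. If the stated test is the only basis for the conclusion, an important excess of death, reinfarction or repeat revascularization could pass as reassurance.

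**Working it through.** **1. Aim against method.** A chi-square test at p<0.05 can come out in three ways.
- *Significant, favouring after-discharge:* this supports superiority, a stronger claim than the one set.
- *Significant, favouring in-hospital:* this shows an excess, but does not say whether it is larger than tolerable.
- *Not significant:* no difference was detected, and nothing has been tested against a margin.

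The aim is written for the situation in which the two risks are similar. There the third outcome is the expected one, and the test is uninformative about non-inferiority.

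**2. The plan's own sample size.** The Introduction gives stays of 8.2 (SD 4) and 6.5 (SD 2.9) days from the centre's retrospective series. With two-sided 5% and 95% power:

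n = (4² + 2.9²)(1.960 + 1.645)² / 1.7² = 109.8, so 110 per group.

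This matches section 5.1. Adding 15% gives 110 × 1.15 = 126.5, close to the stated 125. The sample size therefore stands for length of stay and is not in question.

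**3. How often the chi-square test is non-significant despite a true excess.** The protocol states no design rate for the composite, so the rates below are assumptions. For 20% vs 30% at 125 per arm:
- SE under equality: √(2 × 0.25 × 0.75/125) = 0.0548
- SE under the true rates: √((0.20 × 0.80 + 0.30 × 0.70)/125) = 0.0544
- P(p>0.05) ≈ Φ((1.96 × 0.0548 − 0.10)/0.0544) = Φ(0.135) ≈ 55%

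Exact enumeration over both binomial distributions gives the same figure, and gives the others:

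| True risk, in-hospital vs after-discharge | P(p>0.05), 125 per arm | P(p>0.05), 110 per arm |
|---|---|---|
| 5% vs 10% | 68% | 70% |
| 10% vs 15% | 78% | 79% |
| 10% vs 20% | 40% | 44% |
| 20% vs 25% | 85% | 86% |
| 20% vs 30% | 55% | 60% |

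**4. One possible result.** Suppose 25/125 (20.0%) vs 38/125 (30.4%). The pooled risk is 63/250 = 0.252 and z = 0.104/√(2 × 0.252 × 0.748/125) = 1.89, so p = 0.058. The 95% CI for the excess is 0.104 ± 1.96 × 0.0545, or about −0.3 to +21.1 points. Section 5.2 would call this non-significant, although an excess of 21 points is not excluded.

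**5. Precision with equal true risks, 125 per arm.** The half-width is 1.96 × √(2p(1−p)/125): 5.4 points at p = 5%, 7.4 at 10% and 9.9 at 20%.

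**6. Power to show non-inferiority, 125 per arm, equal true risks, one-sided 2.5%.** Power = Φ(margin/√(2p(1−p)/125) − 1.96). The margins are illustrations, not proposals.

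| Rate | 5 points | 7.5 points | 10 points | 15 points |
|---|---|---|---|---|
| 5% | 44% | 78% | 95% | about 100% |
| 10% | 26% | 51% | 75% | 98% |
| 20% | 17% | 32% | 51% | 84% |

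**The case against.** Five points can fairly be made against this.

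- **The protocol does not say that p>0.05 will be read as non-inferiority.** A reader might infer that it will be. The text does not support that as a statement of intent, because section 5.2 is a general paragraph and does not name the composite. What stands is that the stated test cannot answer the stated aim and that no other rule is given.
- **The SAP is not shown.** A confidence-limit rule and the choice between 6 and 12 months are often left to it, so their absence alone is no finding. The mismatch between 2.4 and 5.2 remains, because an SAP with a proper non-inferiority rule would have to depart from what 5.2 prescribes.
- **The sample size rests on length of stay only.** A reader might call this a defect. It is not one: length of stay is the sole primary outcome, and a secondary outcome need not be powered.
- **A reader might conclude that a real excess would usually go undetected.** That depends on the scenario. It holds for 10% vs 15%, and only just for 20% vs 30%. It fails for 10% vs 20%, where the test misses the excess in 40% of trials.
- **The event rates are weakly anchored.** The Introduction quotes adverse-event rates of 20% and 23% for two complete-revascularization arms of a cited three-arm study, without defining the events or giving the follow-up time. The 20% level is therefore an assumption, as are 5% and 10%. At 5% the precision problem is much milder.

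**Conclusion.** Wrong as written. Sections 2.2 and 2.4 set a non-inferiority aim for safety, and section 5.2 pairs it with a test of difference and no margin. This follows from the text alone and does not depend on any event rate.

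Its practical size does depend on the rates. Over the four scenarios 20% vs 30%, 10% vs 15%, 5% vs 10% and 10% vs 20%, a true excess gives p>0.05 in 40% to 78% of trials at 125 per arm. The 95% CI half-width with equal risks is about 5 to 10 points for rates of 5% to 20%. A non-significant chi-square result would therefore be weak grounds for calling the after-discharge strategy at least as safe. The point concerns a secondary outcome and leaves the primary analysis and its sample size untouched.

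**What to change.** In 2.4 and 5.2, replace the chi-square decision for the composite with the following:
- Report the after-discharge minus in-hospital risk difference with its two-sided 95% CI.
- Name one decisive time point in advance, either 6 or 12 months. The protocol does not favour one over the other.
- Claim non-inferiority only if the upper confidence limit is below a margin fixed in advance and justified on clinical grounds. The margin must not be worked back from what 125 per arm happens to be able to exclude.
- State that p>0.05 is not evidence of non-inferiority.
- Report the power for the chosen margin at the planned size.

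If no margin can be defended, or the trial has little power for it, reword 2.2 and 2.4 so that the aim is to estimate the difference in the safety composite with a 95% CI.

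Either route changes wording only and needs no added patients or procedures. The cost is a weaker safety claim, most clearly under the second route.

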**3. METHODS**

3.1 STUDY POPULATION

Patients aged 18-90 years admitted for STEMI whose reperfusion strategy is PA and who show MVD on coronary angiography, considered as the presence of at least one stenosis ≥ 70% in non-culprit vessel greater than 2 mm in diameter or presence of stenosis ≥ 50% in proximal segment of non-culprit vessel, quantified by QCA, will be prospectively included. Non-culprit stenoses are those identified by the operator as not responsible for STEMI. All patients must meet all inclusion criteria and no exclusion criteria.

3.2 INCLUSION CRITERIA

Candidates shall be those patients who meet all of the following conditions:

1) Patients aged between 18 and 90 years.

2) Presentation of STEMI of less than 12 hours of evolution and candidate for primary angioplasty.

3). Presence of at least ≥ 70% angiographic stenosis in non-culprit vessel > 2mm in diameter, or ≥ 50% in proximal segment of non-culprit vessel measured by QCA.

4). The participant is willing and able to give informed consent for participation in the study.

3.3 EXCLUSION CRITERIA

Candidates must not meet any of the following conditions:

1) Significant left main coronary artery disease.

2) STEMI due to stent thrombosis.

3) Chronic total occlusion of non-culprit vessel.

4) Severe non-culprit vessel stenosis with distal TIMI <3.

5) Non-culprit vessel stenosis not amenable to percutaneous revascularization.

6) Presence of significant valvular heart disease requiring surgery.

7) Killip class IV at the time of presentation.

8) Inability to obtain informed consent.

**4. STUDY PROCEDURE**

4.1 INFORMED CONSENT

The participant should sign the informed consent form before any specific trial procedure is performed.

The written version of the consent and information sheet should be presented to the patient candidate and should include the following information: the exact nature of the trial, the implications and limitations of the protocol, and the risks inherent to such participation. This document should detail that the participant is free to withdraw from the study at any time and for any reason and without prejudice to future care, and without the obligation to give the reason for withdrawal.

The patient shall be allowed as much time as necessary to examine the information and the possibility to question the investigator, his or her general practitioner or other independent parties to decide whether to participate in the study. Written informed consent is obtained by the signature and date of the participant and the person who submitted and obtained the informed consent. The person who obtained the consent must be suitably qualified and experienced, and must have been authorised to do so by the principal investigator. A copy of the signed informed consent shall be given to the participants. The original signed consent document should be retained at the trial site.

4.2 STUDY TREATMENT

Patients will be randomised in a 1:1 computerised fashion to in-hospital CR or after-discharge CR.

4.2.1 In-hospital complete revascularization

In-hospital CR shall be performed at least 24 hours after PA of the culprit vessel. Patients with angiographic stenoses assessed by QCA greater than or equal to 70% will undergo direct PCI and stent implantation, following current recommendations. Those stenoses angiographic lesions (≥ 50%-<70%), will be studied by pressure guidewire to assess their functionality. According to the established FFR values^8^, those lesions with an FFR of FFR≤0,80 will be revascularized.

Demographic, clinical and electrocardiographic variables will be collected on admission, as well as the usual analytical parameters at 24, 48 and 72 hours after STEMI, according to the clinical practice guidelines and the protocol of our department.

Follow-up will be performed at 1 month, 6 months and 1 year in the outpatient clinic and/or by telephone.

4.2.2 After-discharge complete revascularization

After-discharge CR will be performed 4-6 weeks after hospital discharge under optimal medical treatment. Patients with angiographic stenosis assessed by QCA greater than or equal to 70% will undergo direct angioplasty and stent implantation, following current recommendations. Those with moderate angiographic stenosis (≥ 50%-<70%) will be studied by pressure guidewire to assess their functionality. According to the established FFR values^8^, those lesions with an FFR of FFR≤0,80 will be revascularized.

Demographic, clinical and electrocardiographic variables will be collected on patient admission, as well as the usual analytical parameters at 24, 48 and 72 hours after the following current recommendations STEMI, according to the clinical practice guidelines and the protocol of our service.

Follow-up will be carried out at one month, six months and one year in the outpatient clinic and/or by telephone.

**5. SAMPLE SIZE CALCULATION AND STATISTICAL ANALYSIS.**

5.1 Sample size calculation

The calculation of the sample size was based on the mean length of stay between the two strategies obtained in retrospective studies^18-19^ using the Stata 13 "sampsi" programme. Assuming a statistical power of 95% and a significance level of 5%, the sample size for each group is estimated at 110 patients. Taking into account loss to follow-up, the sample size has been increased by 15%, so that 125 patients will be included in each strategy.

5.2 Statistical analysis

Quantitative variables will be expressed as mean ± 1 standard deviation, or as median (interquartile ranges) in the absence of Gaussian distribution. Discrete variables shall be expressed with the frequency distribution. Continuous variables shall be compared with Student's t-test. Discrete variables shall be compared with the X2 test. In all cases a p<0.05 will be considered significant. The statistical package STATA 13.1 will be used for data analysis.

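### The primary comparison of hospital stay is an unadjusted t-test: valid, but it forgoes a modest gain in precision that prespecified baseline adjustment would probably give

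*Protocol*

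**What the plan says.** Section 2.3 gives the primary outcome as "To determine a reduction in hospital stay among patients undergoing complete revascularization during the index admission and on an outpatient basis". Section 5.2 does not single out a primary analysis. It gives one rule for all continuous variables, "Continuous variables shall be compared with Student's t-test", and so that rule covers hospital stay. No covariate is mentioned there, and section 4.2 describes computerised 1:1 allocation without naming stratification factors.

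Three other places bear on what could be adjusted for:

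- The Introduction cites published criteria for identifying low-risk patients, in the context of early discharge: "age <75 years, left ventricular ejection fraction greater than 45%, successful PCI and one- or two-vessel disease".
- Section 4.2.1 says "Demographic, clinical and electrocardiographic variables will be collected on admission", and section 4.2.2 says the same in substance for the other arm. Neither names ejection fraction or PCI success.
- Eligibility (sections 3.2 and 3.3) requires grading of non-culprit stenoses at the index angiography and knowledge of Killip class at presentation, because class IV is excluded. In-hospital revascularization comes at least 24 hours after the primary procedure (section 4.2.1).

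**The concern.** Patients may be aged 18 to 90, in Killip class I to III, and with any ejection fraction. If age, Killip class and extent of disease help to determine how long a patient stays, an unadjusted comparison leaves that variation in the error term. A model with the same factors fixed in advance would then estimate the same difference in mean days with a narrower interval, from the same patients.

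What is at stake is the precision of the primary estimate. The validity of the comparison is not in question.

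**Working it through.** **Inputs**

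- Stay in the two groups: "8.2 ± 4 vs. 6.5 ± 2.9; p<0.001" days, from the centre's own retrospective series (Introduction). Section 5.1 gives no means or SDs and refers to other published studies, so using these figures is an assumption.
- Two-sided significance level 5% and power 95% (section 5.1; the level is stated, the two sides are assumed).
- Stated size: "the sample size for each group is estimated at 110 patients", raised to 125 enrolled.
- R², the share of within-arm variance in stay explained by the covariates: not in the protocol. Assumed range 0 to 0.30.
- Number of covariate terms: p = 4, which allows for age, Killip class, number of vessels and one further factor.

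**Step 1: reproduce the plan's figure.** The difference is 8.2 − 6.5 = 1.7 days, and the variances sum to 4² + 2.9² = 24.41.

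n = (1.960 + 1.645)² × 24.41 / 1.7² = 109.8, rounded up to 110 per group.

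This matches section 5.1. A one-sided 5% level would give 92, which does not. The own-centre figures are therefore a reasonable basis for the rest.

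**Step 2: unadjusted precision.** The average SD is s = √(24.41/2) = 3.494 days. The half-width of the 95% confidence interval is t × s × √(2/n):

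- n = 110: 1.971 × 3.494 × √(2/110) = 0.93 day
- n = 125: 0.87 day

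**Step 3: adjusted precision.** The residual SD becomes s × √(1 − R²). Spending p degrees of freedom multiplies the half-width by about √[(2n − 2)/(2n − 2 − p)], which at n = 110 is √(218/214) = 1.009.

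| Assumed R² | Half-width, 110 per group (days) | Half-width, 125 per group (days) | Power at 110 per group | n per group for 95% power |
|---|---|---|---|---|
| Unadjusted | 0.93 | 0.87 | 95.0% | 110 |
| 0 | 0.94 | 0.88 | – | – |
| 0.05 | 0.91 | 0.86 | 95.9% | 105 |
| 0.10 | 0.89 | 0.83 | 96.7% | 99 |
| 0.20 | 0.84 | 0.79 | 98.1% | 88 |
| 0.30 | 0.78 | 0.73 | 99.1% | 77 |

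The last two columns ignore the small loss of degrees of freedom.

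**Step 4: break-even.** At R² = 0, four covariates widen the interval by about 0.9% with 110 per group. Adjustment pays for itself once R² exceeds about 0.02.

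**Step 5: which covariates are available.** Age and number of diseased vessels are in the cited low-risk criteria and are known at inclusion. Killip class is not in those criteria but must be known to apply the exclusion. Infarct location may be covered by the admission electrocardiographic data but is not named. Ejection fraction and PCI success are not named as collected. The 24, 48 and 72 hour laboratory values can fall after the second procedure in the in-hospital arm and are unsuitable as covariates.

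**The case against.** The case against is substantial, and most of it stands.

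- **The t-test is valid.** With 1:1 allocation and no stratification factors named, no design factor has been left out of the analysis. A reader might infer that chance imbalance in high-risk patients goes uncorrected and so distorts the result. The protocol does not support that: chance imbalance is ordinary sampling error, and the unadjusted interval already allows for it.
- **R² is unknown.** A reader might take the Introduction to show that these factors account for much of the spread in stay. It reports criteria from an outside study for identifying low-risk patients and does not say how much of the variation in stay they explain. Eligibility also limits the covariates: every patient has multivessel disease, and Killip IV is excluded.
- **The gain is small.** At 110 per group and R² of 0.10 to 0.20, the half-width falls by 0.04 to 0.09 day, roughly one to two hours, against a retrospective difference of 1.7 days. The trial is already sized for 95% power.
- **Not every factor is shown to be available.** It would be wrong to say that the trial collects all four criteria the Introduction lists, for the reason given in step 5.
- **Covariates are commonly left to the SAP.** This part does not dispose of the point. The protocol does more than stay silent: it names a test, and a SAP with an adjusted primary model would depart from it.

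**Conclusion.** The point holds as a low-severity improvement in efficiency. Section 5.2 fixes a sound but unadjusted test for the primary outcome, while at least three plausible prognostic factors are known before any second procedure. Adjusting for them would be expected to reduce the half-width from about 0.93 day to between 0.89 and 0.84 day if they explain 10 to 20% of the variance. If they explain nothing, the interval would be about 1% wider.

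These figures rest on the own-centre SDs applying to this trial, 110 evaluable patients per group, four covariate terms and an assumed R². Two stronger statements go too far: that adjustment certainly narrows the interval, because R² is not in the protocol, and that it costs nothing, because it uses degrees of freedom and requires the covariates to be fixed beforehand.

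**What to change.** Amend section 5.2 to state that the primary estimate is the arm difference in mean hospital days, with a 95% confidence interval, from a linear model with robust (heteroscedasticity-consistent) standard errors. Robust errors suit the unequal retrospective SDs of 4 and 2.9 days.

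- Covariates, fixed before the outcome data are examined: age, Killip class at presentation (I versus II–III) and number of diseased vessels at the index angiography.
- Add infarct location and ejection fraction only if they are recorded before randomisation. Because the protocol does not say when randomisation takes place, it should state this too.
- Keep the unadjusted mean difference as a supporting result.

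The cost is a wording amendment, carried through to the SAP. The three core covariates need no new visits, measurements or patients. If a SAP already specifies an adjusted model, the protocol wording need only be brought into line with it.

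### Chi-square is the only test the protocol gives for the 6- and 12-month safety composite; it cannot use partial follow-up and yields no interval for the non-inferiority question

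*Protocol*

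**What the plan says.** Section 5.2 (Statistical analysis) gives one between-group test for categorical data, "Discrete variables shall be compared with the X2 test", and one decision rule, "In all cases a p<0.05 will be considered significant". It names no time-to-event method and does not mention the composite separately.

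Section 2.4 (Secondary outcomes) sets non-inferiority of the outpatient strategy on death, reinfarction or repeat revascularization as the first secondary objective, assessed "at 6 and 12 months follow-up".

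Section 5.1 (Sample size calculation) anticipates incomplete follow-up: "Taking into account loss to follow-up, the sample size has been increased by 15%, so that 125 patients will be included in each strategy".

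Sections 4.2.1 and 4.2.2 give both arms the same contacts, at one month, six months and one year, in clinic or by telephone. The arms differ in when the second procedure takes place: during the index admission, or 4–6 weeks after discharge.

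**The concern.** The composite is a dated event observed over a year. Chi-square reduces it to a yes or no at two time points. A patient last seen event-free at seven months has no 12-month value, and some rule outside the test must supply one. The protocol states none. Stay in the index admission is known at discharge, so the loss foreseen in section 5.1 bears mainly on the outcomes followed to 12 months.

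Two things are at stake. First, the absolute risks, and possibly the difference between arms, depend on how incompletely followed patients are counted. Secondly, section 2.4 asks whether one strategy is no worse than the other. That is judged from an interval for the between-arm difference. A chi-square p-value tests equality and gives no such interval.

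The timing of events is also informative here, because the arms have the second procedure at different times. Two cross-sections hide this.

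**Working it through.** **1. The plan's own figures.** Section 5.1 states: "Assuming a statistical power of 95% and a significance level of 5%, the sample size for each group is estimated at 110 patients". It gives no means or SDs. Assume the input was the centre's own comparison in the Introduction, "8.2 ± 4 vs. 6.5 ± 2.9; p<0.001", with 1:1 allocation (section 4.2):

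- Pooled SD = √[(4² + 2.9²)/2] = √12.205 = 3.49; difference = 8.2 − 6.5 = 1.7 days.
- n = 2 × [3.49 × (1.960 + 1.645)/1.7]² = 109.8, so 110 per group (two-sided 5%, power 95%). The figure reproduces.
- 110 × 1.15 = 126.5. The stated 125 is an increase of 125/110 − 1 = 13.6%.
- Loss that still leaves 110: 1 − 110/125 = 12%. At 15% loss, 125 × 0.85 ≈ 106 remain.

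The tolerated loss is therefore about 12%; 15% is used below as an upper illustration.

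**2. Effect of loss on one arm's 12-month risk.** Assumptions: constant event and loss rates over the year, and loss independent of prognosis. The protocol assumes no event rate. The 20% used here is illustrative; the Introduction reports 20% and 23% for two complete-revascularization strategies in an earlier randomised study.

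Let p be the true risk and l the probability of loss by 12 months if no event occurs. Put h = −ln(1 − p) and c = −ln(1 − l).

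- Event seen before loss: O = h/(h + c) × [1 − e^−(h+c)]
- Followed to 12 months without event: F = e^−(h+c) = (1 − p)(1 − l)
- Lost patients counted as event-free: risk = O
- Patients lost without an event discarded: risk = O/(O + F)

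For p = 0.20 and l = 0.15: h = 0.2231, c = 0.1625, F = 0.80 × 0.85 = 0.680, O = (0.2231/0.3857) × 0.320 = 0.185, and O/(O + F) = 0.185/0.865 = 0.214.

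| True risk | Loss | Counted event-free | Discarded |
|---|---|---|---|
| 20% | 5% | 19.5% | 20.4% |
| 20% | 12% | 18.8% | 21.1% |
| 20% | 15% | 18.5% | 21.4% |
| 10% | 15% | 9.2% | 10.8% |
| 5% | 15% | 4.6% | 5.4% |

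**3. Effect on the comparison, true risk 20% in both arms.** The loss rates by arm are assumptions.

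| Loss, arm A vs arm B | B − A, counted event-free | B − A, discarded |
|---|---|---|
| 12% vs 12% | 0 | 0 |
| 5% vs 15% | −1.0 points | +1.0 points |
| 6% vs 18% | −1.2 | +1.2 |
| 5% vs 25% | −2.0 | +2.1 |

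The sign depends on the counting rule. With equal loss and a real difference, the difference is only rescaled slightly: at 12% loss, 20% vs 23% appears as 2.8 points (event-free) or 3.1 points (discarded) instead of 3.0.

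**4. Size against sampling error.** The 95% half-width of the risk difference is 1.96 × √(2 × 0.2 × 0.8/n): 9.9 points at n = 125 and 10.8 at n = 106.

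**The case against.** Comparing proportions at fixed times is legitimate. Both arms have the same short contact schedule, telephone contact is allowed, and there is no staggered administrative censoring. With equal, non-informative loss and equal risks, the comparison is unbiased. Nothing in the protocol shows that loss will be unequal; the extra attendance in the outpatient arm could improve retention as easily as worsen it. Where bias does arise, it is small beside the sampling error. All of this stands, and it limits the weight of the point.

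A reader might infer more than the document supports in two places. One is that the plan expects 15% of patients to be lost. Section 5.1 gives 15% as an increase in sample size, attached to a length-of-stay calculation. It states no loss rate for the composite. The other is that lost patients must be called event-free or dropped. The protocol sets no rule, imputation before a chi-square test is not excluded, and handling of missing data may be settled in a statistical analysis plan that is not shown.

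What the objection does not remove is that section 5.2 fixes the test. That choice neither uses partial follow-up nor supplies the interval that section 2.4 needs.

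**Conclusion.** The point holds as a weakness in a stated method, of modest size. Under an assumed 20% risk and 12–15% independent loss, the absolute risk in each arm shifts by about 1 to 1.5 points, down or up according to the counting rule; at 5% risk and 15% loss the shift is about 0.4 points. A spurious between-arm difference of about 1–2 points needs unequal loss, which is assumed and not documented. Against a half-width of 10–11 points, this would rarely change a conclusion by itself.

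It would be tempting to conclude that the safety comparison is biased. The documents do not support that, since they give neither an event rate nor loss by arm. The firmer part of the point needs no such assumption: a chi-square p-value cannot carry a non-inferiority statement, and an estimate that allows for censoring, with its interval, is a better choice at little cost.

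**What to change.** In section 5.2, analyse the composite as time from randomisation to first event, censored at last contact. Report Kaplan-Meier risks at 6 and 12 months in each arm, and the risk difference with its 95% CI at each time. Keep chi-square for baseline and procedural categories.

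Add a simple sensitivity analysis for patients lost before 12 months, for example counting them all as event-free and then all as having had an event. Censoring at last contact is unbiased only if loss is non-informative, and Kaplan-Meier estimation does not remove that assumption.

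A Cox hazard ratio is optional and secondary, because the different timing of the second procedure may make the hazards non-proportional.

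Cost: no visit or treatment changes. Event and last-contact dates must be recorded, which the protocol does not state explicitly. The interval makes a non-inferiority judgement possible, but it must still be read against a margin. The protocol gives none, and this change does not supply one.
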